#### Secondary outcomes

There are 13 binary outcomes (encoded as yes/no):

Treatment with narrow-spectrum antibiotics within 48 h from study inclusionTreatment with a single dose of antibiotics onlyTreatment with antibiotics for not more than 48 h (within the first 7 days after inclusion)Treatment with intravenous antibiotics (within the first 7 days after inclusion)De-escalation from broad-spectrum to narrow-spectrum antibiotics (within the first 7 days after inclusion)Escalation from narrow-spectrum to broad-spectrum antibiotics (within the first 7 days after inclusion)Detected aetiology of CAP (within the first 7 days after inclusion)Provision of neuraminidase inhibitors to patients with diagnosed influenza (within the first 7 days after inclusion)Readmission within 30 days after dischargeDeath within 30 days, 90 days, 1 year and 5 years

There are eight quantitative outcomes:Duration of antibiotic use; intravenous and per-oral (in days)Duration of intravenous antibiotics (in days)Duration of broad-spectrum antibiotics (in days)Time from admission to time of pathogen-directed treatment (in hours)Time from admission to time of administration of antibiotic(s) (in hours)Time to appropriate use of isolation facilities (in days)Length of hospital stay (in days)Time from admission to a microbiological sputum test report (FAP *plus* result and/or sputum culture) (in hours)

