## Statistical methods

### Statistical methods for primary and secondary outcomes {20a}

For the first primary outcome, which is a binary outcome capturing whether or not provision of pathogen-directed treatment was given, the comparison between arms will be performed using a logistic regression model. The difference between arms will be quantified by means of an odds ratio or as a difference in probabilities (“a risk difference”). For the second primary outcome, which is a quantitative outcome subject to right censoring capturing the time to pathogen-directed treatment was given, the comparison between arms will be carried out using a semi-parametric or fully parametric event-time model such as the Cox proportional hazards model or accelerated failure time model. Relevant covariate adjustment, including age and sex, will be included in both models.

Secondary outcomes will be analysed using the same two types of models as used for the two primary outcomes. However, for some quantitative secondary outcomes, there will be no right censoring present and, in such cases, linear models or linear mixed models will be fitted, depending on the absence or presence of repeated measurements.

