### Methods in analysis to handle protocol non-adherence and any statistical methods to handle missing data {20c}

As CAPNOR is a pragmatic trial, the main statistical analyses will be carried out according to the intention-to-treat principle using appropriate effectiveness estimands [40]. Specifically, for the two primary outcomes, which are based on an event time, possibly subject to right censoring, the statistical analysis will be based on all patients that were randomised. Likewise, for event-time-derived secondary outcomes, statistical analyses will also be based on the full set of randomised patients. For other outcomes, where missing values may occur, missing values will be imputed using outcome-specific imputation models unless complete-case or available-case analyses could be justified because the missing data mechanisms are missing completely at random or missing at random, respectively.

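### De-escalation, escalation and 48-hour narrow-spectrum use take no account of the antibiotic class at randomisation: the arms stay comparable, but the effects are diluted, imprecise and hard to interpret

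*Protocol article*

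**What the plan says.** Outcomes {12} introduces the list with "There are 13 binary outcomes (encoded as yes/no". Three items in it concern antibiotic class: narrow-spectrum treatment in the 48 hours after inclusion, "De-escalation from broad-spectrum to narrow-spectrum antibiotics (within the first 7 days after inclusion" and "Escalation from narrow-spectrum to broad-spectrum antibiotics (within the first 7 days after inclusion". None says which patients are counted. Another item in the same list does: "Provision of neuraminidase inhibitors to patients with diagnosed influenza".

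Statistical methods {20a} states "Secondary outcomes will be analysed using the same two types of models as used for the two primary outcomes", which for a yes/no outcome means logistic regression, and "Relevant covariate adjustment, including age and sex, will be included in both models". Section {20c} states "the main statistical analyses will be carried out according to the intention-to-treat principle" and adds that "for event-time-derived secondary outcomes, statistical analyses will also be based on the full set of randomised patients". The nearest subgroup in {20b} splits patients by whether and when antibiotics were used, not by spectrum.

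Randomisation takes place when the laboratory receives the lower respiratory sample (Intervention description {11a}, Concealment mechanism {16b}, Implementation {16c}). That is after inclusion, SARS-CoV-2 testing and sputum collection. The Abstract and Background {6a} say that empirical antibiotics are often begun in primary care or soon after arrival at hospital.

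**The concern.** A patient on a narrow-spectrum drug at randomisation has nothing to de-escalate, and a patient on a broad-spectrum drug has nothing to escalate, unless an earlier switch within the 7 days creates the opportunity. Each is close to an automatic no. Conversely, anyone given a narrow-spectrum drug in the first hours is a yes on the 48 h outcome whatever runs beside it or follows. Because that clock starts at inclusion and allocation comes later, the yes can be fixed before the patient has an arm.

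The rapid panel can move these outcomes only in patients who can still have the event. The others add a constant that shrinks the difference and variance that the model could remove but is not told to. Reduced broad-spectrum use is part of the stated hypothesis ({7}). With no account taken of starting class, a null result could mean that the panel changes nothing or that few patients had anything to change.

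**Working it through.** **The plan's own figures.** Sample size {14} gives 470 and 477 per arm at significance level 0.025 and power 0.80. Two-sided calculations return 470 for 50% v 40% and 476 for 0.2 SD. Dropout: 940/0.9 = 1045 and 954/0.9 = 1060. The sizing is not in dispute. It gives no figure for the three outcomes here.

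**Inputs.** 1060/2 = 530 per arm is from the article. The rest is assumed, because the article does not give it: two-sided level 0.05; de-escalation in 40% v 50% of patients who start on a broad-spectrum drug; share starting broad f = 30, 50 or 70%; share untreated at sample receipt u = 0, 30 or 50%. Untreated patients are assumed to split later into broad and narrow starters, and to respond, like the others.

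**Dilution.** If only a share f can have the event, the all-patient rates are f·0.40 and f·0.50, so the risk difference is f·10 points: 3, 5 or 7. At f = 0.5 the rates are 20% v 25%. The odds ratio is (0.25/0.75)/(0.20/0.80) = 1.33, against (0.50/0.50)/(0.40/0.60) = 1.50 among those able to change.

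**Precision.** Unadjusted variance of the difference: [P_C(1−P_C) + P_T(1−P_T)]/n. Stratified on class at receipt, with stratum shares w_k: (1/n)·Σ w_k[p_Ck(1−p_Ck) + p_Tk(1−p_Tk)]. Power = Φ(difference/SE − 1.96). For f = 0.5:

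- Unadjusted: (0.16 + 0.1875)/530 = 0.3475/530, SE 0.0256, power 50%.
- Adjusted, u = 0: 0.5·0.49 = 0.245; SE √(0.245/530) = 0.0215; power 64%.
- Adjusted, u = 0.3: 0.35·0.49 + 0.30·0.3475 = 0.27575; SE 0.0228; power 59%.
- Adjusted, u = 0.5: 0.25·0.49 + 0.50·0.3475 = 0.29625; SE 0.0236; power 56%.

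The difference is 5 points in all four cases; only its precision changes. Restricting to patients on broad-spectrum drugs at receipt recovers the 10 points but uses 530·f·(1−u) per arm.

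| De-escalation power | f = 30% | f = 50% | f = 70% |
|---|---|---|---|
| As written, all patients | 30% | 50% | 69% |
| Adjusted, u = 0 | 44% | 64% | 79% |
| Adjusted, u = 30% | 38% | 59% | 76% |
| Adjusted, u = 50% | 35% | 56% | 74% |
| Restricted, u = 0 | 43% | 64% | 78% |
| Restricted, u = 30% | 32% | 49% | 63% |
| Restricted, u = 50% | 24% | 37% | 49% |

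**Narrow-spectrum within 48 h.** With broad share b and everyone else already on a narrow drug, the rates are (1−b) + 0.2b and (1−b) + 0.3b (20% v 30% among broad starters, assumed). For b = 30/50/70% power is 21/39/63% as written, against 54/76/88% among those not already on a narrow drug. These figures allow for no untreated patients, so they are the favourable end.

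**Escalation.** If events are rare, the removable variance is small. With an assumed 10% v 15% among half the patients, the all-patient rates are 5% v 7.5%. The unadjusted variance is 0.116875/530 and the adjusted one 0.5·0.2175/530 = 0.10875/530. Power goes from 39.1% to 41.5%.

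**The case against.** The strongest reply is that no sentence says all randomised patients form the denominator for these three outcomes. {20c} fixes that set for the primary and event-time-derived outcomes, and a full protocol or analysis plan, not shown, may define the rest. This stands as a caution. The printed definitions nevertheless give no at-risk set where a neighbouring item does, and the covariate sentence, though not exhaustive, names nothing about class.

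Second, the all-randomised difference is a legitimate quantity in a pragmatic trial: the effect of offering the panel to everyone with suspected CAP. This stands fully. A reader might infer that counting everyone is an error and that the main analysis should be restricted to patients at risk. The documents do not support that. The trial declares an intention-to-treat approach, and restriction drops patients whose first dose comes after sample receipt. At f = 50% its power is 49% or 37% with 30% or 50% untreated, no better than the 50% as written.

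Third, a reader might want to replace the 48 h outcome by narrow-only versus any-broad status at 48 h. That has no category for patients who have stopped treatment, been discharged or died by then. Excluding them would condition on something the panel may change, since {18a} counts stopping after a negative result as pathogen-directed.

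Fourth, the outcomes are secondary, and duration of broad-spectrum treatment, also listed, addresses the hypothesis without an at-risk set. That limits the weight of the point. So does the retrospective study cited in {12}, where de-escalation was possible in 77% of patients. If 77% started broad here and nobody was untreated, power would be 75% as written against 82% by starting class.

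**Conclusion.** The concern holds as one of precision and interpretability. Starting class largely, though not absolutely, determines who can have each of the three events, and the article names no adjustment for it. The 48 h outcome can also be settled before allocation.

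A reader might infer bias between the arms. The documents give no ground for it: class at receipt precedes randomisation and is balanced in expectation.

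The size is conditional. With 530 per arm, half starting broad and 40% v 50% among them, a 10-point effect is reported as 5 points with 50% power. Adjustment brings that to 64% with nobody untreated at receipt and to about 56–59% with 30–50% untreated. The gain is smaller when most patients start broad. For escalation it is mainly one of interpretation. The starting mix, the untreated share and the effect sizes are all assumptions. The primary outcomes and their sample size are unaffected.

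**What to change.** - Code antibiotic class at sample receipt in three levels: none, narrow only, any broad.
- Keep all randomised patients as the main analysis set for the three outcomes. Add this pre-randomisation variable to their models as a covariate or stratum, and report the standardised risk difference. This summary also copes with a stratum that has almost no events, such as de-escalation among narrow starters, where a logistic coefficient would be unstable.
- Count narrow-spectrum treatment within 48 h from sample receipt, the point of randomisation and the origin already used for the primary outcomes.
- Report at-risk estimates as supportive: de-escalation among patients on broad-spectrum drugs at receipt, escalation among those on narrow only, and narrow-spectrum use among those not already on a narrow drug. Show the number in each class by arm.

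The cost is one variable coded from the medication charts that {18a} already has extracted, plus a few sentences of analysis text settled before results by arm are examined. No patient is lost from the main analysis and no clinical procedure changes.

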## Abstract

**Background:**

Community-acquired pneumonia (CAP) causes a large burden of disease. Due to difficulties in obtaining representative respiratory samples and insensitive standard microbiological methods, the microbiological aetiology of CAP is difficult to ascertain. With a few exceptions, standard-of-care diagnostics are too slow to influence initial decisions on antimicrobial therapy. The management of CAP is therefore largely based on empirical treatment guidelines. Empiric antimicrobial therapy is often initiated in the primary care setting, affecting diagnostic tests based on conventional bacterial culture in hospitalized patients. Implementing rapid molecular testing may improve both the proportion of positive tests and the time it takes to obtain test results. Both measures are important for initiation of pathogen-targeted antibiotics, involving rapid de-escalation or escalation of treatment, which may improve antimicrobial stewardship and potentially patient outcome.

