As CAP is a potentially serious infection, antibiotics are often given rapidly after presentation to hospital. Due to uncertain microbial aetiology, patients are initially treated with empirical antibiotics that cover a broad range of potential pathogens. The microbiological aetiology of CAP based on conventional routine microbiological testing is achieved in up to 30–40% of cases [12, 15]. With a few exceptions, standard-of-care diagnostic methods are too slow to influence early decisions on antimicrobial therapy. Culture-based techniques are also affected by prior use of antibiotics. Furthermore, sampling from the lower respiratory tract is problematic due to contamination and colonization from the upper respiratory tract flora. The management of CAP therefore largely relies on national empirical treatment guidelines that reflect the prevailing local epidemiology and microbial resistance profiles. Improving microbiological identification and enhancing rapid detection of significant pathogens could have a major impact on the decision-making process, by providing real-time information for treatment decisions within the emergency department. Rapid molecular testing for CAP aetiology may facilitate pathogen-directed treatment, reduce unnecessary antibiotic use, shorten length of hospital stay, improve viral detections and treatment and rationalize isolation facility use. However, limited evidence exists to support its use over standard-of-care microbiological testing. A recent randomised controlled trial (RCT) evaluated the use of molecular testing for respiratory viruses in hospitalized CAP patients in UK [16]. Molecular testing was associated with a greater proportion of patients being treated with brief courses of antibiotics, improved antiviral use, reduced length of stay and was considered safe. Moreover, respiratory viruses were detectable in up to 45% of hospitalized adults with acute respiratory illness [16]. These findings need confirming in other studies that include rapid molecular tests, targeting both viral and bacterial pathogens and with alternate outcome measures.

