### Intervention description {11a}

The trial evaluates the utility of diagnostic tests used for diagnosing the microbiological aetiology in CAP. Blood tests and cultures, urine sample for urine antigen tests, chest x-ray and samples from the respiratory tract are collected in all patients following inclusion. Due to local infection control measures, the patients’ SARS-CoV-2 status needs to be clarified before collecting samples from the lower respiratory tract. Following consent, all patients are tested for their SARS-CoV-2 status. A confirmed case of SARS-CoV-2 is defined as a positive result on the rapid XpertXpress SARS-CoV-2 or SARS-CoV-2/FLU/RSV test run on the GeneXpert system (Cepheid, Sunnyvale, U.A.) or on Cobas SARS- CoV-2 & Influenza A/B test run by the Cobas Liat System (Roche Molecular Systems, Inc., Pleasanton, CA) using naso-/oropharyngeal swab samples. Lower respiratory tract samples are collected after sputum induction or by endotracheal aspiration in both arms. On receipt of the lower respiratory tract sample at the Department of Microbiology, the patients are randomised to the following arms:

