### Concealment mechanism {16b}

The generated allocation sequence is prepared and entered in the eCRF (Viedoc) by staff not involved in the trial. It remains concealed until the moment the patient is randomised, which happens once the Department of Microbiology at HUH receives the respiratory tract sample.

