## Discussion

The COVID-19 pandemic spread to Norway during March 2020 and forced us to adapt to new routines and infection control measures deployed at hospitals and in the society at large. The planned start of the trial was therefore delayed with about 6 months. The time available to collect data and complete inclusions at the emergency department was initially restricted due to shortage of isolation facilities and a large inflow of patients. Initially, each patient is screened for SARS-CoV-2 before an induced sputum sample can be collected at the emergency department, with the subsequent risk of delaying the lower respiratory tract sampling. This is minimized by rapidly sending an oro- or nasopharyngeal swab for analysis by a rapid SARS-CoV-2 test, which provides results within 1 h.

With the national infection control measures, including social distancing, use of facemasks and home office solutions, the number of hospital admissions for lower respiratory tract infections at Bergen Health Trust fell during the first year of the pandemic [24]. This has resulted in slower inclusion rates than anticipated. Finally, COVID-19 and related quarantine among study staff has led to problems with optimal recruitment and timely pursuit of pre-defined study milestones due to absenteeism.

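### Two secondary antibiotic outcomes start their clocks before randomisation, which dilutes any effect of FAP plus and makes a null result hard to interpret

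*Protocol article*

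**What the plan says.** Outcomes {12} lists "Time from admission to time of administration of antibiotic(s) (in hours" among the eight quantitative secondary outcomes and "Treatment with intravenous antibiotics (within the first 7 days after inclusion" among the 13 binary ones. The first clock starts at admission and the second at inclusion. Neither definition is limited to treatment given after allocation.

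Allocation comes later than both. Intervention description {11a} says: "On receipt of the lower respiratory tract sample at the Department of Microbiology, the patients are randomised to the following arms". Concealment mechanism {16b} says the same of the allocation sequence: "It remains concealed until the moment the patient is randomised, which happens once the Department of Microbiology at HUH receives the respiratory tract sample". Before the sample is even taken, "the patients’ SARS-CoV-2 status needs to be clarified before collecting samples from the lower respiratory tract", using a rapid test "which provides results within 1 h" (Discussion). The FAP plus result then reaches the treating staff about 2 h after sampling (Abstract, Methods).

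On the timing of treatment, Background and rationale {6a} says that "antibiotics are often given rapidly after presentation to hospital", and the Abstract adds: "Empiric antimicrobial therapy is often initiated in the primary care setting".

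Both primary outcomes, by contrast, are measured from receipt of the respiratory samples, which is the moment of randomisation. Section {20c} analyses event-time-derived secondary outcomes in all randomised patients.

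**The concern.** FAP plus can change only what happens after the sample reaches the laboratory and, in practice, after the result is phoned. A first antibiotic dose given before then fixes the patient's time from admission to antibiotics, whichever arm follows. An intravenous dose given between inclusion and sample receipt likewise fixes the yes/no intravenous outcome at yes, and no later step-down or stop can reverse it.

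If many patients are in this position, both outcomes pull the arms together. A small or absent difference could then be reported as evidence that rapid testing does not affect antibiotic timing or intravenous use, when the definition left little room for an effect to appear.

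**Working it through.** **Order of events.** Set side by side, the sections give: admission; inclusion and consent; SARS-CoV-2 test (up to 1 h); sputum induction or aspiration; laboratory receipt and randomisation; FAP plus result. The admission clock starts at the first of these and the inclusion clock at the second. Randomisation is the second to last. The interval from admission to randomisation is not stated; the protocol records it only as an exploratory outcome.

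**Figures in the plan.** The plan gives no share of patients treated before sample receipt, no route for early doses, no time to first dose, and no power for these two outcomes. Its sample sizes (470 and 477 per arm at two-sided 0.025 and 80% power) reproduce as 470 and, by normal approximation, 476. They concern the primary outcomes only. The 477 per arm is used below to give a scale.

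**Dilution.** Let f be the share whose value is fixed before FAP plus can act, and d the difference between arms among the rest. The fixed share contributes no expected difference, so the expected overall difference is f*0 + (1-f)*d = (1-f)*d.

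**Assumptions.** f is assumed to lie between 50% and 90%, and it may differ between the two outcomes. For intravenous use, the remaining patients are assumed to have rates of 50% and 40%, a 10-point gap borrowed from the size planned for the first primary outcome. For the time outcome, d is assumed to be 0.2 SD, the size planned for the second primary outcome. Power uses two-sided 0.05 and 477 per arm.

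**Intravenous use.** The overall rates are f + (1-f)*0.50 and f + (1-f)*0.40.

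| f | Rates | Difference | Power | n per arm for 80% power |
|---|---|---|---|---|
| 0 | 50% vs 40% | 10 points | 0.87 | 388 |
| 50% | 75% vs 70% | 5 points | 0.41 | 1251 |
| 70% | 85% vs 82% | 3 points | 0.24 | 2402 |
| 90% | 95% vs 94% | 1 point | 0.10 | 8158 |

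**Time to antibiotic.** With d = 0.2 SD, the overall shift is (1-f)*0.2 SD:

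- f = 0: 0.20 SD, power 0.87
- f = 50%: 0.10 SD, power 0.34
- f = 70%: 0.06 SD, power 0.15
- f = 90%: 0.02 SD, power about 0.05, which is the significance level itself

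A larger effect of 0.5 SD among patients not yet treated would have power 0.97, 0.64 and 0.12 at f = 50%, 70% and 90%.

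**The case against.** A reader might infer that these outcomes mostly record treatment given before randomisation, that they cannot show an effect, or that a null result is built in. The documents do not support this. They say that early treatment is frequent but give no proportion. The effect is exactly zero only if f is 100%: patients untreated when the result is phoned can still have antibiotics started, delayed or withheld, and patients not on intravenous treatment can still start it during the 7 days. Nor is there bias between arms, because treatment before randomisation is balanced in expectation and the tests allow for chance imbalance.

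The intravenous outcome is the weaker half. No section says that early doses are usually intravenous. Its window starts at inclusion, so a dose completed before inclusion is arguably outside it, and treatment begun in primary care does not make it yes.

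It can also be said that, in a pragmatic intention-to-treat trial, (1-f)*d is the real effect of adding the test to emergency-department workflow. That is fair as an estimand, but the resulting number says little about whether the test changes decisions once it is available.

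The rest of the plan limits the damage. These are two of 13 + 8 = 21 secondary outcomes. Duration of intravenous antibiotics, duration of broad-spectrum antibiotics and de-escalation are also listed, and antibiotic use on or before admission is a planned subgroup in {20b}. None of this repairs the two definitions. How patients already on antibiotics at arrival are counted may be settled in the full protocol or analysis plan and is not held against the article.

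**Conclusion.** The point holds as one of sensitivity and interpretation. Both outcomes begin before allocation, and the protocol's own account of early treatment means that some patients will have their values fixed before FAP plus can act. Under the assumed f of 50% to 90%, a 10-point difference in intravenous use among the remaining patients appears as 5 points to 1 point, and a 0.2 SD difference in time as 0.10 to 0.02 SD. Power is then below one half in every case at those effect sizes. These figures rest on an assumed f and an assumed effect among patients not yet treated; the direction of the problem does not. The primary outcomes and the sample size are unaffected.

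**What to change.** - Count both outcomes from sample receipt, that is, from randomisation, as the primary outcomes do.
- Compare time to first antibiotic among patients not on antibiotics at sample receipt. This status is fixed at randomisation, so the comparison stays randomised. Status when the result arrives should not be used, because it falls after allocation.
- For the binary outcome, count intravenous antibiotics given after sample receipt and within 7 days. Read it alongside duration of intravenous treatment, also counted from sample receipt. No further time cut-off is needed.
- Report time from admission to first dose descriptively, not as an outcome of FAP plus.
- Report by arm the share already on antibiotics, and on intravenous antibiotics, at sample receipt, so that readers can see f.

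The cost is mainly wording. Antimicrobial treatment data are already taken from the records ({18a}), and the time of sample receipt is needed for the primary outcomes. The time-to-first-antibiotic comparison will rest on a smaller group. Recruitment is under way and the statisticians are not blinded ({17a}), so the change should be dated, made before analysis, and handled as an amendment under {25}. Clinical management is not affected.
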